**Study synopsis**

Promoting the mental health and psychosocial wellbeing of refugees is a global public health priority. Yet questions remain about the cultural and contextual relevance and effectiveness of psychotherapies applied for specific mental health problems encountered amongst this population. First, the range of mental health problems is wide encompassing co-morbid disorders and forms of distress, yet most interventions focus on the limited outcome of post-traumatic stress disorder (PTSD). Second, western derived methods of intervention draw heavily on cognitive behavioural techniques which on their own may be culturally and contextually alien and more broadly, are not directly congruent with the experiences of refugees. Third, recruitment to studies rarely reflects a systematic approach to identifying persons in need in the community. Finally, interventions tend to be focused on psychopathology (symptoms of distress) rather than on building the capacity for positive adaptation based on an understanding of the psychosocial disruptions that refugees continue to confront following exposure to conflict and displacement. This RCT intervention is innovative in allowing all eligible refugees from a defined catchment area to participate and on focusing specifically on building adaptive capacity based on an established psychosocial model (ADAPT) amongst Burmese refugees (members of the Chin, Kachin, and Rohingya communities) in Malaysia. Specifically, the study will test the efficacy of Integrated ADAPT therapy (IAT), a novel approach that is grounded in the refugee experience rather than on a set of "imported" cognitive behavioural techniques applied to treat traumatic stress in western settings. Our team has spent the past two years in intensive engagement with the communities and relevant stakeholders, using extensive community consultation to ensure the feasibility, acceptability and safety of the project, as well as its contextual and cultural relevance. We have built a strong consensus amongst all stakeholders concerning the value and acceptability of the project. The procedure has been fully manualized, and preliminary training of potential therapists has been very well received. The comparison group will receive CBT as outlined hereunder. Integral to the study is a process for immediate translation and dissemination based on a policy and practice protocol (TPPP), a process that will be greatly facilitated by the extensive engagement, consultation and interaction process that has taken place over the preceding two years with all stakeholders relevant to the communities in which the study will be implemented

**Introduction**

It is estimated that 60 million persons have been exposed to mass conflict and displacement in the contemporary world, the largest number since WW II [1]. Questions remain about the cultural and contextual relevance and effectiveness of psychotherapies applied in the refugee mental health field [2]. Specifically, past intervention studies have been limited by (a) selection biases making it difficult to evaluate the needs of the community and the best way to engage with them and offer opportunities to obtain treatment; (b) a focus on trauma events and immediate living difficulties rather than on the longer term disruption of psychosocial support systems; (b) the use of CBT techniques derived from western models of intervention; (c) a singular focus on reducing symptoms, particularly of post-traumatic stress disorder (PTSD) and depression [3, 4]; (d) a relative under-emphasis on the explicit task of building resilience, capacity to deal with ongoing challenges, and the promotion of adaptation to the new environment; and (d) lack of follow up (most studies being limited to follow-up periods of 6 months or less); (e) failure to include an active comparison treatment and non-binding treatment providers [3, 5].

We have developed a novel psychotherapeutic approach which focuses on the stressors and adaptive difficulties caused by the undermining of the core psychosocial systems during the course of the refugee experience. Our approach, referred to as Integrative Adapt Therapy (IAT) is based on the Adaptation and Development After Persecution and Trauma (ADAPT) model [6]. The formulation, refinement, and cultural adaptation of IAT has been described previously [7].

The ADAPT model postulates that five psychosocial domains are disrupted by the sequence of events associated with the refugee experience, namely safety/security, bonds/networks, access to justice, roles/identities, and existential meaning. The model reflects a growing consensus in the field that ecosocial conditions (comprising social, cultural, economic, spiritual and existential components) shape the effects of trauma and ongoing daily living difficulties in determining the ability of individuals to adapt. Where the ecosocial environment and supportive psychosocial systems are severely disrupted, experiences of trauma and adversity are more difficult to accommodate, increasing communal and individual levels of distress and functional impairment. Importantly, the ecosocial environment itself undergoes major changes as refugees traverse the sequential phases of conflict, flight, transition and resettlement [8]. Our studies show that the disruptions of the psychosocial systems underpinning the ADAPT model play an important role in shaping mental health and adaptation outcomes and contribute not only to a wide array of comorbid mental disorders (CMDs) but also to difficulties in functioning and capacity to adapt to the new environment [9].

IAT has several advantages over conventional approaches: (a) it authenticates the refugee’s experience by tailoring the intervention to the lived experience of psychosocial disruption; (b) it is adapted to each culture and context, a process achieved by a standardized period of community consultation and research using qualitative methods (focus groups, informant interviews); (c) rather than being primarily trauma- or symptom-focused, IAT explicitly is designed to build adaptive capacity based on the individual and collective experiences of refugees, drawing on the ADAPT model; (d) the integrated process of assessment and therapy therefore aims to create a strong foundation of trust, respect and mutual understanding, thereby promoting the therapeutic alliance; (e) the integrated approach adds to the contextual validity of the intervention by focusing on key changes that have occurred during the period of conflict, flight, transition and resettlement that together have impacted on the psychosocial support systems of the community; (f) the focus is on the potential to use self-help strategies to overcoming ongoing obstacles and restoring psychosocial equilibrium insofar as possible; (g) while novel in its starting point, the therapy builds on and incorporates techniques shown to be effective in past interventions including problem-solving, behavioural activation, conflict resolution, interpersonal skills training and trauma narration, ensuring the capacity for task shifting, that is, engaging counsellors drawn from refugee groups to undertake the process [10] . Consistent with the contemporary focus and the ADAPT theory, we adopted a transdiagnostic approach in which we included a range of symptoms of CMDs frequently observed amongst refugees [11]. Specifically, we include the full range of symptoms of PTSD, Complex PTSD (CPTSD), Major Depressive Disorder (MDD), Generalized Anxiety Disorder (GAD), and Persistent Complex Bereavement Disorder (PCBD) [12, 13].

In summary, IAT aims to integrate four essential goals: to provide a clear but flexible theoretical framework that makes sense of the refugee experience; to translate these principles into the real life challenges and response patterns relevant to individuals within their culture and context; to use the understanding and insight gained as a motivator for individuals to make adaptive changes; and to provide them with the evidence-based techniques to develop adaptive strategies that are flexible enough to deal with ongoing and future challenges as they evolve.

This paper outlines the protocol for a randomized controlled trial undertaken to test the efficacy and feasibility of IAT by comparing it to an active psychological treatment, CBT^[[1]](#footnote-1)^ amongst Myanmar refugees in Malaysia. In general, refugees in Malaysia face recurring threats of arrest, detention, and deportation due to insecure residency in addition to poverty, limited educational opportunities and access to healthcare and basic services. Our study aims therefore were to test the following hypotheses: (1) that both CBT and IAT would achieve improved outcomes on all symptom measures; (2) that IAT would show a consistent pattern of superiority in outcomes compared to CBT; and (3) that IAT would demonstrate superiority compared to CBT in promoting resilience and reducing adaptive stress related to erosion of the five ADAPT pillars. The improvements will be evident immediately post-treatment and at 12-month follow-up^[[2]](#footnote-2)^.

**Study design**

In this single-blind two-armed RCT, participants who are UNHCR recognized refugees will be recruited from a clustered, multistage epidemiological study conducted amongst Myanmar refugees (from Chin, Kachin, and Rohingya communities) concentrated in and around Kuala Lumpur, the capital of Malaysia. Recruitment continued serially until we achieved the projected number of participants based on our power analysis estimates (see hereunder).

**Study participants**

Participants will comprise male and female adults (18 years of age or older) who are members of the Chin, Kachin, and Rohingya communities. Inclusion criteria are (a) meeting criteria for at least one of the included CMDs (PTSD/CPTSD, MDD, GAD, and PCBD)[11]; (b) witnessed or experienced at least one traumatic event related to mass conflict; and (c) endorsed at least one stressor on the ASI. Exclusion criteria are than 18-years of age; intellectually disabled or cognitively impaired based on obvious indicators of disability; presence of overt psychosis (as assessed using the WHO mhGAP protocol) [14].

All participants will be assessed at baseline, immediately post-treatment, and at 12-month follow-up. Figure 1 shows the flow of participants through the trial.

Figure 1. Flow Diagram

Post Intervention

Initial assessment for eligibility

Informed consent

Baseline assessment

Randomization

N=331

CBT: 6 Weekly sessions

of 45 minutes

IAT: weekly sessions

of 45 minutes

Enrolment

Allocation

6 weeks Post-treatment

assessment

Follow-up

12 months follow-up

assessment

*Sample size*

The International Society for Traumatic Stress Studies (ISTSS) has provided guidance concerning the magnitude of outcome differences that should be regarded as clinically meaningful in comparing one active psychotherapy over another in the trauma field [15]. Based on this guide, we estimated that a minimum of 150 participants were needed in each arm to achieve a moderate effect size of 0.50 and a design effect of 1.5, based on 80% power and a two-tailed 5% significance level. This calculation assumed an attrition rate of 50% in view of the pattern of substantial resettlement to third countries that could occur based on recent precedence over the period of follow-up.

*Randomization and masking*

Eligible participants will be randomized to either the IAT or CBT arm. Participants who meet the inclusion criteria will then be randomized based on a 1:1 ratio using a computer-generated randomization sequence. An off-site research assistant will oversee the randomized assignment, a process fully concealed from the counsellors who will be informed about treatment assignments via the trial coordinator. Refugees will be blind to their diagnostic status but not their treatment condition. The statistician involved in data management, analysis and interpretation of results will be blind to the participants’ treatment condition.

Following randomization, participants will attend the intervention at established NGO community centres which are trusted places of safety based on the provision within Malaysian law that affords designated NGOs legal immunity against government interference.

Field Research Personnel

*Community Intervention Teams (CIT)*

There will be three community intervention teams comprising 24 personnel, 8 personnel for each ethnic group (with an equal number of male/female counsellors within each team). All counsellors speak fluent Rohingya and Burmese and will treat participants in either the IAT or CBT arm. For cultural reasons, female counsellors will be assigned to female/male participants, whereas male counsellors will be assigned only to male participants. Each team will be trained in both IAT and CBT. To minimize cross-contamination between the treatment conditions, the trainings will be conducted separately for each ethnic group; additional care will be taken not to imply preference for one therapy over the other.

*Community Assessment Team: (CAT)* will comprise Rohingya- and Burmese speaking assessors trained (independently of CIT) specifically in administering the assessment battery at baseline, immediately post-treatment, and at 6- and 12-month follow-up. All team members will be trained in the importance of maintaining concealment, and the two teams (CIT and CAT) will be located separately.

Competency rating, supervision, and treatment fidelity

Inter-rater reliability of assessments (90% concordance in assigning cases) will be required for each assessment team member. Treatment fidelity will be assessed by independent clinical psychologists and supervisors trained in IAT or CBT based on observations of a 10% random sample of counsellor’s sessions (10 sessions per counsellor) using a checklist and narrative commentary aimed at ensuring systematic delivery of each component of the respective therapies. The supervisor will then rate each session as “satisfactory” or “unsatisfactory” based on this evaluation. Further training and fidelity checks will be provided for counsellors assigned an unsatisfactory rating. The treatment adherence evaluation has been tested in other psychotherapy. Trained counsellors from the three ethnic groups will complete rigorous competency evaluations and will be required to demonstrate a high level of fidelity in implementing treatments under the supervision of bilingual clinical supervisors.

Adaptation and delivery of treatment modules

The treatment manuals will be translated and adapted for the Rohingya, Chin, and Kachin refugees drawing on our extensive work conducted on IAT. All treatment sessions will be conducted across community offices in close proximity to the residences of the participants. Details of the process of cultural adaptation and qualitative testing have been described elsewhere [7].

*Integrative Adapt Therapy (IAT)*

As indicated, IAT is grounded in the five psychosocial pillars of the ADAPT model.[7] Refugees participating in IAT are encouraged to reflect on past and ongoing experiences that have disrupted the psychosocial foundations of their societies, their families and themselves during the trajectory of mass conflict, upheaval, displacement, flight, transition, and resettlement. They are assisted in making connections between these experiences and patterns of maladaptive personal responses that are of major concern to them in their emotional, cognitive, behavioural and interpersonal lives. By making sense of their own response patterns within the context of the disruptions experienced by themselves, their families and the refugee society as a whole, IAT sets the stage for participants to identify more precisely what changes they need to make to improve their lives. They are offered a range of skills such as problem solving and cognitive restructuring to promote their adaptive capacities in a concrete manner in order to address contemporary problems in their lives and to prepare them to navigate future challenges. As an example, refugees who experience uncontrollable episodes of aggression may be guided to draw on their experiences to make connections between their overwhelming feelings of anger and the injustices they and their families have been subjected to (Pillar III of the ADAPT model). Anger then becomes less alienating and incomprehensible returning a sense of control to the refugee who is motivated to learn strategies (cognitive, behavioural, interpersonal) that will assist in anticipating, preventing and curtailing episodes of aggression, thereby improving the sense of control and the participant’s interpersonal relationships. A similar process is followed in relation to other pillars of the ADAPT model.

*Cognitive Behavioural Treatment (CBT)*

The culturally adapted CBT condition included six core treatment strategies: psychoeducation, stress management, problem-solving, behavioural activation, cognitive reappraisal, and strengthening social support. Two criteria are applied in selecting these techniques: they include “common elements” that are evidence-based in treating symptoms of common mental disorders in populations affected by adversity; and the package is well suited to application by lay counsellors based on the principle of task-shifting [10]. Each strategy is introduced sequentially over the course of six sessions and each session built on the previously learned techniques. The emphasis is on the application of techniques to manage distressing and dysfunctional emotions and behaviours, using a range of materials and homework practice to ensure that participants mastered the skills. Although the same techniques are used in both therapies, the major difference is that the core ADAPT theme is not included in the CBT arm. Instead, the treatment is presented as an intervention to manage stress and interactions with others. Where appropriate, traumatic events are inculcated in the procedure. For example, in the session focusing on cognitive re-appraisal, a refugee who reports feelings of guilt and shame following sexual assault is taught cognitive re-appraisal techniques to address these maladaptive thoughts and feelings.

Primary outcomes

*Posttraumatic Stress Disorder, Complex PTSD, Major Depressive Disorder*

The Refugee Mental Health Assessment Package (RMHAP) [11] includes a comprehensive set of indices assessing trauma exposure, postmigration living difficulties, common mental disorders, and the Adaptive Stress Index [16], the latter recording stress arising from erosion of the five ADAPT pillars. The core modules of the RMHAP – those assessing CMDs and the ASI have been adapted and tested extensively in refugee groups [11, 16]. Revised Harvard Trauma Questionnaire (HTQ) [17] will be used to measure torture, trauma and DSM-5 PTSD symptoms.

We will use the relevant modules of the RMHAP to assess symptoms of PTSD, CPTSD, MDD, GAD and PCBD, all according to DSM-5 with the exception of CPTSD which was based on ICD-11 [11]. Symptoms are rated on a four-point scale based on how frequently they are experienced (1=not at all, 2=a little bit, 3=quite a lot, 4=extremely); the two highest frequency categories are regarded as indicating a clinically significant endorsement of the symptom. In all interviews, participants are required to complete the full symptom list for each disorder without applying skip rules. Responses were recorded on an electronic tablet thereby reducing risk of data management errors. Past psychometric analyses of both categorical and dimensional measures of the five CMDs each yielded sound internal consistency, test-retest reliability, and concurrent validity with gold-standard diagnostic measures [11, 18, 19]. A mean score was calculated for each diagnostic category and used in pre- and post-treatment outcome analyses.

*Resilience*

The Connor-Davidson Resilience Scale (CDRS) [20] consists of 25 items assessing five resiliency factors: (1) personal competence, high standards, and tenacity; (2) trust in one’s instincts, tolerance of negative affect and strengthening effects of stress; (3) positive acceptance of change, and secure relationships; (4) control; and (5) spiritual influences. The measure is the most widely used in trauma-affected populations including refugees and past studies have shown high levels of internal consistency, test-retest reliability, and convergent validity [21, 22]. Items are assessed on a 5-point Likert scale that ranges from ‘not true at all’ (scored 0) to ‘true nearly all the time’ (scored 4). Total scores range from 0 to 100; a mean score was calculated based on all items, with higher scores reflecting greater resilience.

*Adaptive Stress (ASI)*

The Adaptive Stress Index [16] comprises five individual scales, each consisting of an empirically derived set of items assessing the individual’s capacity to cope with stress arising from erosion of each ADAPT pillar: ASI-1 (12 items assessing safety and security); ASI-2 (14 items assessing traumatic losses and separations); ASI-3 (13 items assessing injustice); ASI-4 (11 items assessing role and identity disruptions); ASI-5 (14 items assessing existential meaning). Each item is scored on a 4-point Likert scale (0=not at all, 1=a little, 2=quite a lot, 3=extremely) with a possible score ranging from 0 to 3; a mean score was calculated for each ASI scale based on all scored items. The ASI as a whole as well as its five constituent scales have been subjected to extensive psychometric testing across several refugee groups [16]. Interpersonal functioning will be assessed using the Inventory of Interpersonal Problems Short Form, a brief index of individuals’ self-reported difficulties in interpersonal relationships [23].

Secondary Outcomes

Symptoms of Generalized Anxiety Disorder and Persistent Complex Bereavement Disorder will be assessed using the relevant modules of the RMHAP, as indicated above. Functionality will be assessed using the abbreviated version of the World Health Organization Disability Assessment Schedule (WHO-DAS) [24], attachment styles will be assessed using Close Relationship Scale [25] , sense of injustice will be assessed using a brief index of moral injury [26], and anticipatory traumatic stress will be assessed using a brief index drawing on our previous research in Timor-Leste [27]. A mean score was calculated for each diagnosis and used in pre and post-treatment outcome analyses.

*Adverse events reporting*

We will apply the Unwanted Events and Adverse Treatment Reaction Checklist for Psychotherapy [28] and implement procedures – developed with the community – for mitigating risk of adverse reactions using culturally adapting monitoring questions. We will ensure timely action including referral to local services if any events occur. Specifically, we will partner with UNHCR, UNHCR-affiliated health partners, Kuala Lumpur Hospital in training our team in established protocols for responding to indicators of suicidality and violence in the community.

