**Analytic plan**

Statistical analysis: Planned T-tests and chi-squared tests will be applied to assess differences between the two treatment groups. Intention to treat analysis (ITT) will be applied to examine differences in baseline and post-treatment scores. All outcomes will be treated as continuous. A random-effect model will be used to estimate treatment effects including five assessment time points and counsellor ID as random effects to account for within-person correlation across time and between-correlation by counsellor. A post-hoc analysis using the baseline measurement as a covariate will be implemented. Gender, age, and other relevant sociodemographic characteristics will be examined separately as covariates. Missing data will be imputed using chain equations command in Stata which allows for pooling of data according to Rubin’s rules.

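### The stated sample-size inputs call for about 189–192 per arm, not 150; at 50% attrition, 150 per arm gives about 70% power rather than 80%

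*Protocol*

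**What the plan says.** The protocol's Sample size paragraph (under Study participants) states that "a minimum of 150 participants were needed in each arm to achieve a moderate effect size of 0.50 and a design effect of 1.5". The same sentence sets the target power at 80% and makes the test two-sided at the 5% level. The sentence after it deals with loss to follow-up: "This calculation assumed an attrition rate of 50% in view of the pattern of substantial resettlement to third countries". So 150 per arm is presented as a figure that already includes both the design effect and the attrition allowance.

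Three other statements bear on the calculation:

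- Randomization and masking: participants are "randomized based on a 1:1 ratio using a computer-generated randomization sequence".
- Analytic plan: "All outcomes will be treated as continuous".
- Study design: "Recruitment continued serially until we achieved the projected number of participants based on our power analysis estimates", which ties the end of recruitment to this calculation.

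Figure 1 shows 331 randomised. The paragraph names no test and gives no baseline or repeated-measures correlation.

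**The concern.** Every input needed to reproduce the figure is printed, and the result is not 150. The protocol therefore claims 80% power for a moderate effect that its own assumptions do not support.

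This matters for two reasons. Recruitment was governed by the calculation. And the comparator is an active therapy that, by the protocol's own account, uses the same techniques without the core ADAPT theme, so a null result is plausible. A reader who takes the power statement at face value would put the chance of missing a true effect of 0.50 at 20%. Under the stated assumptions it is about 30% with 150 per arm, or about 26% with 331 in total.

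**Working it through.** **Inputs, all from the protocol.** Standardised effect d = 0.50; two-sided alpha 0.05; power 0.80; design effect 1.5; attrition 50% (Sample size). Allocation 1:1 (Randomization and masking). Continuous outcomes (Analytic plan). Numbers: 150 per arm (Sample size) and 331 in total, about 165.5 per arm (Figure 1).

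**1. Attempt to reproduce 150.**

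Analysable per arm before inflation, normal approximation: n = 2(z₀.₉₇₅ + z₀.₈₀)²/d² = 2(1.960 + 0.842)²/0.25 = 62.8, rounded up to 63. The two-sample t-test gives 63.8, rounded up to 64.

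Randomised per arm = n × design effect / (1 − attrition):

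- t-test: 64 × 1.5 = 96; 96 / 0.5 = **192** (384 in total)
- normal approximation: 63 × 1.5 = 94.5; 94.5 / 0.5 = **189** (190 if rounded up at each step)

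The requirement is 26–28% above 150 (189/150 = 1.26; 192/150 = 1.28). Rounding or choice of formula does not explain that.

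**2. Power actually available at 50% attrition.**

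Effective n per arm = N × 0.5 / 1.5. Power and detectable effect are for an unadjusted two-sample t-test.

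| Randomised | Effective n per arm | Power for d = 0.50 | d detectable with 80% power |
|---|---|---|---|
| 150 per arm | 50 | 0.697 | 0.57 |
| 331 in total | 55.2 | 0.740 | 0.54 |
| 192 per arm | 64 | 0.801 | 0.50 |

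The normal approximation gives 0.705 and 0.747 in the first two rows.

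**3. When the 80% claim would hold.** The trial needs 96 retained per arm:

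- 150 per arm: maximum attrition 1 − 96/150 = 36%
- 331 in total: maximum attrition 1 − 96/165.5 = 42%

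**4. Other routes to 150.**

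| Route | Per arm |
|---|---|
| One-sided 5%, normal approximation: n = 2(1.645 + 0.842)²/0.25 = 49.5, rounded up to 50; 50 × 1.5 / 0.5 | 150 |
| Design effect omitted: 63 or 64 / 0.5 | 126–128 |
| Attrition omitted: 63 or 64 × 1.5 | 95–96 |
| Square root of the design effect (not a standard inflation) | 154–157 |

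The only standard route found that lands on 150 is a one-sided 5% test, which conflicts with the stated two-tailed level. The document does not show that this is how the figure was obtained.

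**The case against.** **The shortfall depends on attrition reaching 50%.** This stands. The 50% is a planning allowance for resettlement over the follow-up period, and the protocol also tests superiority immediately post-treatment. It gives no attrition figure for that time point. If attrition there were 20–30% (my assumption), unadjusted power would be 88–84% with 150 per arm and 91–87% with 331. A reader might infer that the trial is underpowered throughout; the documents do not support that.

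**The planned model may be more efficient than a two-sample comparison.** This stands in part. The Analytic plan describes a random-effect model over repeated assessments. With baseline adjustment, the requirement scales by (1 − r²). A baseline correlation of about 0.47 (r² = 1 − 150/192) would bring it to 150 per arm, and about 0.37 (r² = 1 − 165.5/192) would suffice for 331 in total. But the protocol states no correlation, does not use one in the sample-size paragraph, and calls the baseline-covariate analysis post-hoc. The stated figure is not rescued, but 70% and 74% must be labelled as unadjusted.

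**Imputation.** Multiple imputation is planned, but it does not by itself restore the information lost with the missing half, and the protocol itself sized the trial for that loss.

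**Two stronger readings should be set aside.**

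- A reader might infer that 331 in Figure 1 contradicts the plan. It does not: 150 per arm is a stated minimum (300 in total), 331 exceeds it, and the past-tense recruitment sentence suggests 331 is the number achieved.
- A reader might infer that attrition was added as a 50% mark-up. That gives 96 × 1.5 = 144, which does not match 150 and fits worse than a one-sided test. Neither explanation is proven.

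**Conclusion.** The power statement is wrong as written: the listed inputs require about 189–192 per arm, and the document gives no assumption that closes the gap at a two-tailed 5% level.

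The size of the error is moderate: 10 percentage points of power at the stated minimum of 150 per arm, and about 6 points at 331. These figures rest on an unadjusted comparison, the design effect of 1.5, and attrition at the assumed 50%. The consequence falls mainly on the 12-month comparison. No estimate, analysis or type I error rate is affected. It is an error in a headline design claim, and correcting it costs only wording.

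**What to change.** Revise the Sample size paragraph in one of two ways, leaving enrolment unchanged.

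1. Replace the 80% claim with what the stated assumptions deliver. For example: *Assuming 50% attrition and a design effect of 1.5, an unadjusted comparison at a two-sided 5% level has about 70% power for an effect size of 0.50 with 150 randomised per arm (80% power for 0.57), and about 74% with 331 randomised in total (80% power for 0.54).* Adding that 80% power for 0.50 is kept with attrition up to about 36% or 42% respectively would help the reader interpret the post-treatment comparison.

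2. If 150 came from a calculation with a further assumption, such as a baseline correlation, state that assumption and its value and show that it gives 150 at a two-tailed 5% level. If the calculation was in fact one-sided, say so and take the first option, because the protocol specifies a two-tailed level.

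The cost is a few sentences and a less favourable power statement. No participants, visits or analyses are added.
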